### Study outcomes

This study will focus exclusively on the short-term follow-up outcomes for women and their offspring. Specifically, short-term outcomes are defined as events occurring during hospitalization, with particular attention to the following aspects:Complications: Assessment of complications related to postpartum stroke, including the risk of stroke recurrence, cardiovascular complications (such as heart failure and arrhythmias), and infection risks (such as pulmonary or urinary tract infections)Medical interventions: Documentation of treatments administered during hospitalization, including antiplatelet or anticoagulant therapies, antihypertensive medication, antibiotic use, and physical therapy interventions, to evaluate their effectiveness and patient responseChanges in health status: Close monitoring of overall health fluctuations during the hospital stay, including neurological function, blood pressure control, heart rate stability, and emotional state, to comprehensively assess health variations throughout treatment

#### Primary outcome

These are the following: For Aim 1, composite unfavorable outcome defined as *mRS* > 2 or EQ-5D index score < 0.7 at follow-up; for Aim 2, recurrent strokes confirmed by neuroimaging; and for Aim 3, the Apgar scores of newborns and results from Ages & Stages Questionnaires, Third Edition (ASQ-3) at follow-up.

#### Secondary outcome

These are the following: For Aim 1, unfavorable functional outcomes at discharge; for Aim 2, strokes occurring during subsequent pregnancies; and for Aim 3, the occurrence of intrauterine death, stillbirth, or critical illnesses requiring hospitalization in the offspring (see Table 3).

**Table 3 Tab3:** Outcome measures^a^

• **Women**

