**Design:**

This study is a retrospective, observational, nationwide, multicenter research project planned to include 400 ASPP patients from 36 centers across 22 provinces in China, from 2015 to 2024. ASPP is defined as acute ischemic or hemorrhagic stroke during pregnancy or within 6 weeks postpartum, confirmed by neuroimaging. Two matched groups will be included for comparison: 400 pregnant/puerperal participants without a stroke history and 400 nonpregnant/puerperal participants with a recent stroke, matched by age and/or stroke etiology.

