## Background

Acute stroke in pregnancy and puerperium (ASPP) is a rare but serious complication associated with high morbidity and mortality in women of childbearing age. The incidence of pregnancy-associated stroke is estimated at 30 per 100,000 pregnancies and appears to be rising, with an inhospital mortality rate of 4.2% for pregnant women experiencing acute stroke [1–3]. Compared to their nonpregnant counterparts, pregnant women with acute stroke face a higher risk of deterioration and more complex management needs [4]. Regarding the long-term risk of ASPP, women with pregnancy-associated stroke have lower risks of recurrent ischemic stroke and mortality compared to those with strokes unrelated to pregnancy. Furthermore, the risks of recurrent intracerebral hemorrhage and cerebral venous thrombosis do not differ significantly, and recurrent stroke during subsequent pregnancies remains rare [5].

Previous studies have predominantly utilized large-scale national healthcare data and the International Classification of Diseases (Tenth Revision, Clinical Modification) (ICD-10-CM) to examine the incidence rate and risk factors for ASPP [6–8]. Although these population-based studies benefit from larger sample sizes, they often lack detailed data, which hinders a comprehensive exploration of risk factors and the identification of prognostic predictors and range of variables collected, such as laboratory results, neuroimaging characteristics, and management strategies. This limitation hampers the comprehensive exploration of risk factors and the identification of prognostic predictors. As women with ASPP are generally young and likely to achieve good recovery, no long-term follow-up studies have been conducted to assess their long-term functional outcomes. Additionally, it remains to be explored whether ASPP is solely a short-term risk factor that does not affect a woman’s risk of stroke in future pregnancies or throughout her life.

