When pregnant women experience acute strokes, the systemic circulatory system may be severely affected, causing significant fluctuations in blood pressure that impact fetal blood flow [9]. These dramatic changes in fetal blood flow can lead to adverse intrauterine effects, such as fetal distress and neonatal asphyxia, potentially resulting in unfavorable outcomes for the offspring, thereby affecting the prognosis of the offspring [10]. However, no study has explored the impact of acute stroke in pregnancy and puerperium on the offspring and their future development. Besides, AMI (acute myocardial infarction) in pregnancy and ASPP may share a common pathophysiological mechanism, where their onset can be predisposed by physiological changes related to a hypercoagulable state, vascular endothelial remodeling, and alterations in insulin and lipid metabolism [11]. Only a few studies have explored the maternal and fetal outcomes of patients with AMI during pregnancy, and no study has assessed the future development of their offspring, mirroring the current research status of ASPP [12]. Therefore, it is important to understand the maternal and neonatal outcomes of these patients.

Establishing a cohort based on patients with ASPP is essential for addressing the aforementioned issues. Due to the rarity of ASPP, obtaining a sufficient sample size necessitates a nationwide, multicenter study. In 2020, the European Stroke Organisation proposed an international, multicenter, prospective cohort study to comprehensively explore ASPP patients [13]. However, no related study results have been reported to date. Moreover, the study protocol did not include the future development of the offspring of ASPP patients. The objectives of the ASPP study are as follows: (1) to explore the risk factors of ASPP and predictors of its prognosis; (2) to evaluate the risk of recurrent strokes, particularly during subsequent pregnancies, in ASPP patients; and (3) to assess the prognosis of offspring of ASPP patients.

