Grouping of non-ASPP participants is as follows:Non-ASPP participants include two matched control groups: The first group consists of participants in the pregnancy or postpartum period without a history of stroke (pregnancy/postpartum non-stroke group); the second group consists of nonpregnant or non-postpartum participants who have recently experienced a stroke (nonpregnant stroke group).Matching criteriaFor the pregnancy/postpartum non-stroke group, controls will be matched to ASPP cases in a 1:1 ratio based on age (±2 years) and hypertension history, with the latter stratified into preexisting hypertension, pregnancy-induced hypertension, or no hypertension.For the nonpregnant stroke group, a 1:1 matching strategy will be applied using age (±2 years), stroke etiology (classified by TOAST criteria), and preexisting hypertension status.Classification of pregnancy-related etiologies is as follows:Postpartum vascular diseasePregnancy-related hypercoagulable statesPregnancy-induced hypertensionPreeclampsiaAmniotic fluid embolismMatching of nonpregnant/postpartum patientsAge matching (±2 years)Matching based on stroke etiology, such as cardiogenic stroke, atherosclerotic stroke, small vessel disease stroke, and other identifiable causes (e.g., intracerebral hemorrhage)Health status and comorbidities, including common comorbidities such as cardiovascular disease, hypertension, and diabetesLifestyle factors, such as smoking and alcohol consumption historyDiscussion of the impact of pregnancy-related etiologiesEtiological characteristics, such as thrombosis resulting from pregnancy-related hypercoagulable states, hemodynamic changes caused by postpartum vascular disease, and hypertensive lesions associated with preeclampsiaPhysiological changes: Physiological changes during pregnancy, such as increased blood volume, blood pressure fluctuations, and alterations in coagulation mechanismsPsychological and social factors: Assessing the unique challenges faced by pregnant women in coping with stress, anxiety, and other mental health issues, as well as their potential impact on stroke occurrenceImpact assessment: When comparing ASPP patients with nonpregnant stroke patients, the influence of pregnancy-related etiologies on stroke recurrence rates and long-term prognosis will be clearly delineated.

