### Sample size estimates

Formal power calculations were conducted using parameters from Chinese population studies. Based on the Health Study of Chinese Shanghai Women reporting a 1.45-fold stroke risk increase with high parity (≥ 5 pregnancies), we calculated a requirement of 268 ASPP cases and 804 matched controls (1:3 ratio) to detect similar associations (*α*= 0.05, 80% power) [15]. For longitudinal analysis of stroke recurrence, 456 ASPP cases are needed to identify a 40% risk reduction (90% power), anchored to China-specific stroke incidence data. Our target enrollment of 400 ASPP patients balances statistical rigor and feasibility, accounting for a 20% attrition rate, multicenter recruitment capacity (36 centers, ~ 11 cases/center/year), and subgroup analyses (e.g., cerebral venous thrombosis).

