### Statistical analysis

Descriptive statistics will express continuous variables as means (±standard deviation) or medians (interquartile range) and categorical variables as proportions. Chi-square tests or Fisher’s exact tests, along with Student’s *t*-tests or Wilcoxon rank-sum tests, will be used to compare demographics and clinical characteristics between cases and controls. Chi-square tests will compare dichotomous outcomes, while *t*-tests or Mann-Whitney *U*-tests will compare quantitative outcomes. Kaplan-Meier curves and log-rank tests will evaluate survival analyses, with Cox proportional hazard models calculating hazard ratios and 95% confidence intervals (CIs). Multivariate logistic regression will identify independent predictors, and linear or generalized linear models will assess the impact of ASPP and other factors on delivery outcomes and the ASQ-3 results. First, logistic regression will calculate odds ratios and 95% CIs for recurrent stroke. Subgroup analysis will evaluate potential differences in endpoints for predefined subgroups (such as gestational hypertension, preeclampsia, HELLP syndrome, gestational diabetes, trimester, and type of delivery). Multiple imputation will address missing baseline data, with a *p*-value of < 0.05 considered statistically significant.

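### Stroke in a subsequent pregnancy, which Aim 2 emphasises, will yield very few events, and the plan's general chi-square rule for dichotomous outcomes is unreliable at such counts

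*Protocol article*

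**What the plan says.** The second objective in the Background is "to evaluate the risk of recurrent strokes, particularly during subsequent pregnancies, in ASPP patients", and the abstract gives the same emphasis. Under Secondary outcome the corresponding endpoint is "for Aim 2, strokes occurring during subsequent pregnancies".

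The Background gives two pieces of information on frequency. In words, "recurrent stroke during subsequent pregnancies remains rare". In numbers, "The incidence of pregnancy-associated stroke is estimated at 30 per 100,000 pregnancies". The second is a general incidence, not a recurrence risk in women who have already had a stroke.

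The Sample size estimates section refers to "Our target enrollment of 400 ASPP patients" and allows for 20% attrition. The abstract adds the comparison groups: "400 pregnant/puerperal participants without a stroke history and 400 nonpregnant/puerperal participants with a recent stroke". For the second of these, "a 1:1 matching strategy will be applied using age" and other factors. No number of later pregnancies, event count or power is given for this outcome; the recurrence calculation concerns recurrent stroke overall.

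Under Statistical analysis, Fisher's exact test appears beside chi-square for demographics and clinical characteristics. The next sentence covers outcomes and gives no exact alternative: "Chi-square tests will compare dichotomous outcomes". The section also names Kaplan-Meier, log-rank and Cox methods, and logistic regression for recurrent stroke. The significance threshold is 0.05.

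**The concern.** The article provides an exact fallback for baseline comparisons, where counts will mostly be adequate, and states none for outcomes, where one emphasised endpoint is described as rare. If the general rule is applied to that endpoint, two errors are possible. A handful of strokes in one group may be declared significant by an approximation that does not hold at those counts. Or zero or one event with p > 0.05 may be taken as reassurance that ASPP carries no excess risk in a later pregnancy, although the data would still be compatible with a risk many times the background rate. Women and clinicians planning a further pregnancy would be the readers of that result.

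**Working it through.** **Inputs from the protocol article.** 400 ASPP patients and 20% attrition (Sample size estimates), so 400 × 0.8 = 320 evaluable; 30 per 100,000 = 0.0003 per pregnancy (Background); comparison groups of 400 each (abstract); threshold 0.05, taken as two-sided.

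**Assumed, because the article gives no figure.** Later pregnancies per woman, 0.1 to 1.0; risk of stroke per later pregnancy in women with previous ASPP, 0.03% to 2%.

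The article prints no event count for this outcome, so there is no figure to reproduce.

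**1. Expected events in the ASPP group** = women × later pregnancies per woman × risk per pregnancy.

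| Women | Later pregnancies per woman | Risk per pregnancy | Expected events | Chance of none |
|---|---|---|---|---|
| 400 | 1.0 | 0.03% (printed) | 0.12 | 89% |
| 320 | 1.0 | 0.03% (printed) | 0.10 | 91% |
| 400 | 0.3 | 1% (assumed) | 1.2 | 30% |
| 320 | 0.5 | 1% (assumed) | 1.6 | 20% |
| 400 | 1.0 | 1% (assumed) | 4.0 | 2% |
| 400 | 1.0 | 2% (assumed) | 8.0 | under 1% |

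Four expected events in 400 women need 4/400 = 1% per pregnancy with every woman pregnant again. That is 0.01/0.0003 = 33 times the printed rate.

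**2. Does the chi-square approximation hold?** In a 1:1 table the smallest expected cell is half the total number of events. It stays below the usual minimum of 5 until there are 10 events over both groups.

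**3. Does the choice of test matter?** Uncorrected chi-square = N(ad − bc)² / (product of the four margins).

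- 4 against 0 in 400 per group: 800 × (4 × 400)² / (400 × 400 × 4 × 796) = 4.02, p = 0.045. Yates-corrected p = 0.133; Fisher's exact p = 0.124.
- 1 in 40 against 0 in 160 later pregnancies (illustrative denominators): 200 × (1 × 160)² / (40 × 160 × 1 × 199) = 4.02, p = 0.045. Fisher's exact p = 40/200 = 0.20. One stroke would cross the 0.05 line.

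**4. Do the other named methods help?** With no events in one group, ordinary logistic regression has no finite odds ratio and the Cox model no finite hazard ratio, so neither is a remedy.

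**5. What can a comparison detect?** Exact power of Fisher's test for 1% against 0.03% is 20% with 400 pregnancies per group and 10% with 320. For 1% against 0.6% it is 3% and 2%.

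**6. What does a zero count exclude?** The Clopper-Pearson 95% upper limit for 0 in n is 1 − 0.025^(1/n).

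- n = 160 (assumed): 1 − 0.025^(1/160) = 2.3%, about 76 times the printed incidence.
- n = 400: 0.9%, about 31 times.

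**The case against.** The strongest reply is that no sentence assigns chi-square to this outcome by name. The rule is generic, time-to-event and logistic methods are also listed, and the article may have condensed away an exact alternative that a statistical analysis plan contains. The outcome is secondary, no power is claimed for it, the article itself calls such events rare, and it nowhere says that a null result would be read as no excess risk. All of this is fair and limits the weight of the point. It does not remove it: the article does state a rule for dichotomous outcomes, mentions the exact test one sentence earlier for another purpose only, and the other listed methods fail in the same situation.

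Three stronger readings are tempting, and the documents do not support them.

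- A reader might infer that the protocol's figures predict zero to four events. The printed rate gives about 0.1. The upper end rests on an assumed 1% risk and one later pregnancy for every woman.
- A reader might infer that the study cannot answer its question. The stated aim is to evaluate a risk, and a proportion with an exact interval does that, if imprecisely. What the counts cannot support is an informative comparison between groups.
- A reader might infer that unequal numbers of later pregnancies push the chi-square error rate above 5%. Enumerating two binomials at an assumed 1% risk gives 8.8% for 160 against 40 pregnancies, but 2.8%, 1.8% and 4.1% for 160 against 120, 100 and 80, and 3.2% for 160 against 160. At the printed rate, 160 against 40 gives 1.1%. The approximation errs in either direction, depending on the split and the risk.

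**Conclusion.** The point holds as a moderate, easily corrected weakness in the stated analysis. From the article's only rate, about 0.12 events are expected in 400 women with one later pregnancy each. Even at an assumed 1% the expectation is at most 4, and the 2% end of the assumed range, with every woman pregnant again, gives 8. Throughout the range up to 4, chi-square is unreliable and can give a different answer from an exact test (0.045 against 0.124).

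The conclusion rests on two things: the recurrence risk is low, which the Background says in words without a number, and the generic rule for dichotomous outcomes would govern this one. The number of later pregnancies is unknown; fewer than one per woman makes the counts smaller still. It would be wrong to say that the protocol names chi-square for this outcome.

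**What to change.** In the Statistical analysis section:

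1. Report stroke in a subsequent pregnancy as the number of events over the number of later pregnancies, with an exact (Clopper-Pearson) 95% interval, and give the upper limit explicitly when the count is 0 to 2.
2. For any group comparison of a sparse dichotomous outcome, use Fisher's exact test or another exact or penalised method (for example Firth-type logistic regression) in place of chi-square.
3. State that a non-significant difference in this outcome will not be read as absence of excess risk.

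The cost is a few sentences, plus recording the number of later pregnancies in each group at follow-up as the denominator. The downsides are that this emphasised part of Aim 2 becomes mainly descriptive, and that exact tests are somewhat conservative.

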***Short-term outcomes***
▪ Inhospital mortality
▪ Unfavorable functional outcome (assessed by mRS and EQ-5D) at discharge^b^
▪ Duration of hospitalization

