### Data collection and management

Baseline data collection will be conducted through the electronic medical record (EMR) system of the participating centers. If certain variables are not recorded in the EMR, they will be collected retrospectively through telephone interviews. Table 2 presents the variables to be collected at baseline. A specialized secure database (CRF, case report form) will be established to facilitate the collection of standardized data from different centers. All data will be anonymized to ensure privacy, and each patient included in this study will be identified by an identity number. General variables (such as demographics, medical history, and medication history) and pregnancy- or puerperium-associated variables (including data on delivery and offspring-related variables) will also be collected for non-ASPP participants.

**Table 2 Tab2:** Baseline variables

• **Demographics**
▪ Age
▪ Ethnic: Han or other
• **General clinical variables**
▪ Date of admission and discharge
▪ BMI (calculated based on prepregnancy weight and height data)
▪ Previous or current smoking
▪ Previous or current drinking
▪ Previous or current drug abuse
▪ NIHSS and/or mRS at admission and discharge
▪ Blood routine index: RBC, WBC, PLT, etc.
▪ Blood biochemical index: TC, HDL-C, etc.
▪ Coagulation function index: TT, PT, FIB, APTT, etc.
▪ Other blood index: lupus anticoagulant, anticardiolipin antibodies, etc.
• **Medical history**
▪ Hypertension (if with record maximal SBP and DBP)
▪ Diabetes
▪ Migraine
▪ Polycystic kidney disease
▪ Cerebral vascular disease (if with record etiology)
▪ Myocardial infarction or angina
▪ Congestive heart failure
▪ Known atrial fibrillation or flutter
▪ Valvular heart disease
▪ Hypercholesterolemia
▪ Pulmonary embolism

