***Long-term outcomes***
▪ **Developmental status** (assessed by ASQ-3) **at follow-up**^d^
▪ Critical illness (if with record etiology)^e^

*mRS* modified Rankin Scale, *EQ-5D* EuroQol five dimensions questionnaire *ASQ-3* Ages & Stages Questionnaires, Third Edition

^a^Short-term outcomes are defined as events occurring during hospitalization, while long-term outcomes are defined as health status within 1-year post-discharge and during follow-up. All participants will be followed up through telephone interviews. The initial follow-up is scheduled to take place between December 2024 and February 2025. The follow-up phase will consist of three rounds, each lasting 3 months and conducted every 3 years

^b^Functional outcomes will be assessed using the modified Rankin Scale (mRS), with an mRS score greater than 2 defined as an adverse outcome

^c^Neonatal asphyxia will be assessed using Apgar scores at 1, 5, and 10 min, with scores of 8–10 defined as no asphyxia, 4–7 as mild asphyxia, and 0–3 as severe asphyxia

^d^The ASQ-3 categorizes developmental status into five subdomains: (1) Communication, (2) gross motor, (3) fine motor, (4) problem-solving, and (5) personal-social. Based on scores in each subdomain, results will be classified as “above,” “close to,” or “below” the threshold

^e^Critical illness is defined as the offspring requiring hospitalization due to a diagnosed disease, including neurological diseases, cardiovascular diseases, gastrointestinal diseases, respiratory diseases, urological diseases, hematological and immunological diseases, and other major disorders

Functional outcomes will be assessed using the modified Rankin Scale (mRS), with an mRS score greater than 2 defined as an adverse outcome. An independent assessment team, composed of professionals who did not participate in the patients’ treatment, will be responsible for evaluating functional outcomes during follow-up to ensure objectivity and reduce potential bias. Members of this assessment team will receive systematic training to ensure their proficiency in the assessment criteria and procedures of the mRS and EQ-5D questionnaires, thereby enhancing the reliability of the assessment results.

Specific assessment criteria include the following:

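### The Aim 1 secondary outcome at discharge is defined inconsistently and partly has no data source: Table 3 names mRS and EQ-5D, its footnote b uses mRS > 2 alone, and Table 2 collects NIHSS and/or mRS

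*Protocol article*

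**What the plan says.** The Secondary outcome section of the protocol article gives, for Aim 1, "unfavorable functional outcomes at discharge". Table 3, under women's short-term outcomes, names the instruments: "Unfavorable functional outcome (assessed by mRS and EQ-5D) at discharge". That row carries footnote b, which reads "Functional outcomes will be assessed using the modified Rankin Scale (mRS), with an mRS score greater than 2 defined as an adverse outcome". The running text below the table repeats this, and neither place gives an EQ-5D criterion.

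The Primary outcome section uses a different rule for the later time point: "composite unfavorable outcome defined as *mRS* > 2 or EQ-5D index score < 0.7 at follow-up". No rule combining the two instruments is given for discharge.

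On data, the section Data collection and management says "Baseline data collection will be conducted through the electronic medical record (EMR) system of the participating centers" and refers to Table 2 for the variables. The only functional or severity item there is "NIHSS and/or mRS at admission and discharge"; EQ-5D is not in Table 2. The same section adds the fallback: "If certain variables are not recorded in the EMR, they will be collected retrospectively through telephone interviews". The assessor-guided EQ-5D is described only within the follow-up assessment.

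On timing, participants are included from January 2015 to November 2024, and the first telephone follow-up runs from December 2024 to February 2025.

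**The concern.** A named secondary outcome should have one definition and a data source that can supply it. Here the row label, its footnote and the collection list each describe something different. Discharges in 2015 to 2024 cannot be revisited, so an instrument not used at the time cannot be supplied from the record.

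Two things are at stake. First, whether a woman can be classified, and how, may depend on which scale her hospital recorded and which definition the analyst applies. That would weaken comparison of discharge outcome rates across the 36 centers. Second, the fallback does not separate facts a participant can report, such as smoking, from ratings of her state on one past day. A remembered discharge rating is likely to be colored by present health, and present health is the Aim 1 primary outcome. Recalled values could therefore make discharge status and follow-up status look more closely related than they were.

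**Working it through.** **Step 1. The sources side by side.**

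| Place in the article | mRS at discharge | EQ-5D at discharge | NIHSS at discharge |
|---|---|---|---|
| Table 3, discharge row | yes | yes | no |
| Table 3, footnote b, and text below | yes, > 2 is adverse | no | no |
| Table 2 (what is collected) | optional (and/or) | no | optional (and/or) |

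No two rows agree. Footnote b is the only one that gives a usable cut-off.

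**Step 2. What can be classified from the record.** Two definitions are compared: footnote b (mRS > 2), and the either-or rule carried over from the primary outcome (mRS > 2 or EQ-5D index < 0.7). The second is an assumption about what the row label may intend.

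| In the hospital record | Footnote b | Either-or rule |
|---|---|---|
| mRS > 2 | unfavorable | unfavorable, EQ-5D not needed |
| mRS 2 or less | favorable | undetermined without EQ-5D |
| NIHSS only | undetermined | undetermined |
| neither scale | undetermined | undetermined |

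A record with NIHSS alone satisfies Table 2 but gives no outcome under either definition. A record with mRS is fully classified under footnote b. Under the either-or rule, no woman could be classified as favorable from the items listed.

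**Step 3. Length of recall if the telephone fallback is used.** Inputs: inclusion from 1 January 2015 to 30 November 2024, and first telephone round from 1 December 2024 to 28 February 2025. The inclusion date stands in for the discharge date, because no length of stay is given. Days are divided by 365.25.

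- Longest gap: 3,622 days to the start of the round = 9.9 years; 3,711 days to its end = 10.2 years.
- Shortest gap: 1 day to the start; 90 days to the end, about 3 months.
- Mean gap, assuming events are spread evenly over the 3,621-day window: (3,621/2 + 1)/365.25 = 5.0 years to the start; (3,621/2 + 90)/365.25 = 5.2 years to the end.
- Share with a gap above 1 year, calling on 15 January 2025 (46 days after inclusion closes): 1 − (365.25 − 46)/3,621 = 0.91.
- Share above 5 years: 1 − (1,826.25 − 46)/3,621 = 0.51.

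The last three lines rest on even accrual, which the article does not state.

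**Step 4. What cannot be computed.** The article does not say how many centers recorded mRS, NIHSS or neither at discharge. The number of unclassifiable women and the size of any recall bias therefore cannot be estimated from it.

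**The case against.** The strongest reply is that the outcome is already workable. Footnote b prints mRS > 2, Table 2 lists discharge mRS, and the data come from the medical record. On that view EQ-5D in the row label is a slip, and mandatory fields belong to the full protocol, which is not shown. The Discussion also concedes recall and information bias.

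Much of this stands. Three stronger readings that a reader might infer are not supported:

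- *That the discharge outcome can only be filled by recall.* A recorded discharge mRS needs none. Even for EQ-5D, the fallback sentence sits in a paragraph about baseline variables and does not name it. The document supports saying that discharge EQ-5D has no contemporaneous source, not that women will be asked to rate a day 10 years past.
- *That recall would occur in the same call as the follow-up assessment.* The baseline-completion interviews are not dated. The first follow-up round is merely the only dated contact near that time.
- *That predictors such as admission NIHSS or laboratory values will be obtained by telephone after the outcome.* The article does not say which variables will be completed this way, and multiple imputation is also planned for missing baseline data.

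What the reply does not remove is the disagreement between the row label, its footnote and Table 2. These are all statements in the article, not details left to another document. Nor does a general admission of recall bias limit which variables may be recalled.

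**Conclusion.** The point holds in a limited form. The discharge outcome for Aim 1 is defined in two ways within Table 3, and neither matches what Table 2 guarantees. EQ-5D at discharge has no contemporaneous source, and a record with NIHSS alone gives no outcome. Any discharge mRS or EQ-5D supplied through the fallback, if taken at the first dated round, would be recalled over up to about 10 years, and about 5 years on average under even accrual.

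The extent depends on how often discharge mRS is in the records, which is unknown. Where it is recorded and footnote b is applied, the problem disappears. This concerns a secondary outcome and does not affect the definition of the primary one. It should be corrected before the discharge outcome is analyzed.

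**What to change.** 1. Define the discharge outcome as mRS > 2 taken from the hospital record, in line with footnote b, and delete EQ-5D from the discharge row of Table 3.
2. In Table 2, list mRS at discharge as its own item, with NIHSS as an addition and not a substitute.
3. In Data collection and management, exclude mRS, NIHSS and EQ-5D at admission or discharge from telephone completion, and record the source of every value in the case report form.
4. Report missing discharge mRS as missing, by center. Do not treat it as covered by the planned multiple imputation: that is stated for missing baseline data, and discharge mRS is an outcome. Imputing it would be a separate decision needing its own justification.

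The cost is a few lines of wording and one source field. The downside is more missing discharge outcomes, possibly concentrated in centers that recorded only NIHSS, and no discharge EQ-5D. The article offers no valid way to measure the latter.
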